**11-2. Criteria for handling subjects**

1) Ineligible cases

Cases that violate the selection criteria or the exclusion criteria will be considered as ineligible cases.

2) Cases of GCP non-compliance

Subjects who are not in compliance with GCP, such as not obtaining proper informed consent, shall be considered as GCP noncompliance cases.

3) Discontinuation or dropout

Subjects who withdrew consent or discontinued the study due to the occurrence of adverse events or other reasons judged by the investigator, etc. are considered as discontinuation cases. Subjects who stop coming to the hospital for reasons not directly related to the clinical trial are also considered as dropout cases. Subjects who have received 8 or more doses of the investigational drug will not be treated as discontinuation or dropout cases.

4) Cases of treatment violations and incomplete evaluation data

Cases of violation of dosage and administration, concomitant drug use, etc. are considered as cases of violation of treatment, and cases of incomplete evaluation data are considered as cases of incomplete evaluation data.

5) Other problem cases

For unanticipated problem cases other than 1) to 4) above, the Clinical Trial Coordinating Committee will discuss them with the investigator who conducts the clinical trial and statistical analysis experts as necessary, and decide how to handle them in terms of statistical analysis. The impact of this handling on the results will be reported in the summary report.

**11-3. Data handling standards**

If there is a discrepancy between the observation and test dates specified in the protocol and the actual observation and test dates, each item will be used only when it is measured within the following criteria. In addition, the number of days shall be 0 days from the scheduled visit date as specified.

1) PS

[figure not shown]
*: Same day of the week as the registration date is acceptable.

[figure not shown]
2) Body weight

[figure not shown]
3) Vital sign

*: Same day of the week as the registration date is acceptable.

**: Including maintenance dose

[figure not shown]
4) General blood tests (on the day of blood collection)

[figure not shown]
5) Thyroid function tests (on the day of blood collection)

6) Tumor marker (on the day of blood collection)

[figure not shown]

[figure not shown]
7) Urinalysis

[figure not shown]
8) CT or MRI

9) Antigen-specific antibody immunoreaction test (date of blood collection)

[figure not shown]

10) Regulatory T cells test (date of blood collection)

[figure not shown]

[figure not shown]

11) Pharmacokinetics

[figure not shown]
12) Immunopotentiation effectiveness test (date of blood collection)

13) Genetic analysis

[figure not shown]

**11-4. Analysis items and methods**

Detailed analysis methods are described in the "Statistical Analysis Plan" and "Pharmacokinetic Analysis Plan" to be prepared separately.

1) Safety

(1) Number of DLT cases

The number of DLTs and the incidence rate of DLTs per treatment group in Phase Ia are shown.

(2) Occurrence of adverse events and adverse reactions

Adverse events that occurred in Phase Ia and Phase Ib are summarized in the table. All adverse events and adverse drug reactions are summarized by the MedDRA basic terms and by major organ category, and the number and percentage of adverse events for each treatment group are shown.

(3) Gene analysis

Exploratory studies will be conducted as necessary.

2) Efficacy

(1) Efficacy in eliminating regulatory T cells

Summary statistics are calculated for each treatment group.

(2) Antigen-specific antibody immune response

To be investigated in an exploratory manner for each treatment group.

(3) Anti-tumor effect

The number of responders and the percentage of responders (response rate) will be calculated for each treatment group.

(4) Progression-free survival (PFS)

Progression-free survival is calculated using the Kaplan-Meier method.

(5) Overall survival (OS)

Overall survival is calculated using the Kaplan-Meier method.

(6) Immunostimulatory effect

To be examined on an exploratory basis as necessary.

(7) Gene analysis

To be explored as necessary.

In addition, the relationship between regulatory T-cell elimination effect and anti-tumor effect, antigen-specific antibody immune response, etc. will be explored.

3) Pharmacokinetics

(1) Plasma Mogamulizumab concentration

Plasma concentrations of Mogamulizumab will be listed and descriptive statistics for each dose will be shown; plasma concentration trends of Mogamulizumab will be plotted graphically as individual subject data and mean (+ standard deviation) versus blood collection time on a real and log scale.

(2) Mogamulizumab pharmacokinetic parameters

Calculate the pharmacokinetic parameters for each subject as indicated in "8-3-1 Definition of primary endpoints 1) Phase Ia Part (2) Pharmacokinetics" and calculate descriptive statistics for each dose.

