[Phase Ib] The patient population will be divided into 20 patients in each group, each of whom will receive one dose and 0.1 mg/kg, the highest dose among the doses that were found to be well tolerated in Phase Ia (one step below the MTD or 1.0 mg/kg if the MTD has not been reached). The dose should be administered intravenously once a week for 8 consecutive weeks. However, if the dose of 0.1 mg/kg was the only dose that was found to be tolerated in Phase Ia, a dose of 0.1 mg/kg will be used in Phase Ib for 20 patients in each group.

<Rationale for Dose Setting>

If the safety and regulatory T-cell effects of Mogamulizumab in solid tumors are confirmed by this study, it is assumed that a drug that releases immunosuppression by a mechanism different from that of Mogamulizumab may be used in combination with Mogamulizumab in the future. In such a case, the possibility of autoimmune reactions would be higher than with single-agent administration of Mogamulizumab. Therefore, the low dose group was set at 0.1 mg/kg, the lowest dose established in Phase Ia, in order to obtain data over a wide dose range for confirming regulatory T-cell removal efficacy. The low-dose group was set at 0.1 mg/kg.

In the Phase Ib study, the high-dose group and the 0.1 mg/kg group were used in the Phase Ib study.

For subjects who showed SD or higher in the regulatory T-cell test, antigen-specific antibody immunoreactivity test, or diagnostic imaging after 8 doses, if the subject wished to receive maintenance dosing of the study drug and if the investigators determined that maintenance dosing of the study drug was appropriate, the investigator or other appropriate personnel would administer the study drug to the subject. If the subject wishes to receive maintenance dosing of the investigational drug and the investigator determines that maintenance dosing is appropriate, maintenance dosing of the investigational drug is allowed every 4 weeks after 12 weeks until the discontinuation criteria are met.

[figure not shown]
Phase Ia: Starting at 0.1 mg/kg, dose escalation to 0.5 mg/kg and 1.0 mg/kg if tolerability is confirmed.

Phase Ib: Among the treatment groups that were found to be well tolerated, a high-dose group and two 0.1 mg/kg groups (if 0.5 mg/kg was the MTD in Phase Ia, one 0.1 mg/kg group) were administered. Enrollment to be 20 patients in each group.

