**7-7. Dosing methods**

When administering the drug, ensure that the drug meets the "7-7-1. Administration Criteria" and does not conflict with the "7-7-2. Postponement of Administration Criteria" and "7-7-3. Criteria for discontinuation of administration”.

The investigational drug must be started within 2 weeks of case enrollment.

[Phase Ia] Either 0.1 mg/kg, 0.5 mg/kg or 1.0 mg/kg dose is administered intravenously over 2 hours once a week for a total of 8 doses.

[Phase Ib] If tolerability up to 1.0 mg/kg was confirmed in Phase Ia, 0.1 mg/kg or 1.0 mg/kg18

or 0.1 mg/kg or 0.5 mg/kg if tolerability up to 0.5 mg/kg is confirmed, or 0.1 mg/kg if tolerability up to 0.1 mg/kg is confirmed, administered intravenously over 2 hours once a week for a total of 8 doses.

[Common to both Phase Ia and Phase Ib]

1) Maintenance dose

The ninth and subsequent doses of the investigational drug will be administered every 4 weeks as maintenance doses, provided that "7-8. Criteria for Drug Discontinuation" are not violated.

2) Dosing Interval

The dosing interval should not be shortened until 8 doses have been administered. After the 9th dose, dosing may be postponed for up to 2 weeks, and the next dose may be shortened by up to 2 weeks.

3) Pre-treatment at the time of administration

Since reactions associated with injection are expected to occur in almost all patients, 30 to 50 mg of diphenhydramine and 300 to 500 mg of acetaminophen should be taken 30 minutes prior to administration of the study drug. In addition, 100 mg of hydrocortisone should be administered intravenously before the second dose of diphenhydramine 30-50 mg and 300-500 mg of acetaminophen after the first dose. Dosage may be adjusted according to age and symptoms.

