**7-8. Maintenance dose implementation criteria**

If all of the following criteria are met, maintenance dosing of the investigational drug to the subject concerned will be permitted until "7-7-3.

1) Maintenance dosing can be started within 6 weeks after the 8 doses.

2) If the subject shows an SD or greater in regulatory T-cell elimination and antigen-specific antibody immunoreactivity or RECIST after treatment with the investigational drug.

3) The subject wishes to receive maintenance dosing of the investigational drug

4) The investigator determines that maintenance administration of the investigational drug is appropriate.

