Overall Survival (OS) is defined as the period from the start date of study drug administration to death from any cause. For patients who survived without confirmed death, the date of last confirmed survival shall be considered as the date of last confirmation of survival, and for patients who were lost to follow-up, the date of last confirmed survival shall be considered as the date of discontinuation.

2) Phase Ib

(1) Tumor reduction effect

See "8-3-2. Definition of Secondary Endpoints 1) Phase Ia".

(2) Progression-free survival

See "8-3-2. Definition of Secondary Endpoints 1) Phase Ia".

(3) Overall survival

See "8-3-2. Definition of Secondary Endpoints 1) Phase Ia".

(4) Determination of recommended doses for Phase II and beyond

Recommended doses for Phase II and beyond will be determined based on a comprehensive review of the safety and efficacy in eliminating regulatory T cells in Phase Ib.

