**10-1-2 Definition of harmful events and side effects (harmful events with a negative causal relationship)**

An adverse event is any unfavorable medical event that occurs in a subject receiving an investigational drug. In other words, any unwanted or unintended signs (including abnormal changes in laboratory values), symptoms, or illnesses that occur when the investigational drug is administered, regardless of whether or not there is a causal relationship with the investigational drug. In addition, adverse drug reactions (adverse events for which a causal relationship cannot be denied) are all adverse events other than those judged to have a "no relationship" causal relationship to the investigational drug.

Signs, symptoms, and abnormal changes in laboratory values associated with a disease (diagnostic name) shall be treated as adverse events with the diagnostic name. However, if an atypical or extremely severe sign or symptom occurs in the disease, the individual sign or symptom as well as the diagnosis should be treated as an adverse event.

The observation period for adverse events will be from the date of the first dose of study drug to 12 weeks after the last dose. However, for Grade 3 or higher non-hematologic toxicity, the observation period for adverse events shall be up to 24 weeks.

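### Crude adverse-event percentages per dose group rest on observation windows whose length depends on response and on stopping, so they can mislead the Phase Ib dose choice if either differs by dose

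*Protocol*

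**What the plan says.** Section 11-4 1)(2) covers the adverse events of Phase Ia and Phase Ib. It summarises all events and reactions by MedDRA term and organ class, and "the number and percentage of adverse events for each treatment group are shown". It names no time window, no split between the first eight doses and maintenance, and no rate per unit of time.

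The window is set in section 10-1-2: "The observation period for adverse events will be from the date of the first dose of study drug to 12 weeks after the last dose". An exception follows: "for Grade 3 or higher non-hematologic toxicity, the observation period for adverse events shall be up to 24 weeks". Both are tied to the individual subject's dosing and not to a fixed date.

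Section 7-7 sets the initial course, "administered intravenously over 2 hours once a week for a total of 8 doses". Under section 7-1, maintenance then "is allowed every 4 weeks after 12 weeks until the discontinuation criteria are met". Section 7-8 opens it to subjects with regulatory T-cell elimination and an antibody response, or stable disease or better on RECIST, if the subject wishes it and the investigator agrees.

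Adverse events are a Phase Ib primary endpoint (section 8-1-2). Section 8-3-2 uses them for dose selection: "Recommended doses for Phase II and beyond will be determined based on a comprehensive review of the safety and efficacy in eliminating regulatory T cells". When Phase Ib has two dose groups, section 7-5-2 allocates at random by minimization on carcinoma, with 20 subjects per group (section 7-6-2).

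**The concern.** A percentage per group treats every subject as having had the same opportunity to show an event. Here that opportunity depends on what happens after allocation. A subject who responds or stays stable may go on to maintenance, and is then dosed and watched for longer. A subject who stops early is watched for less time. If the doses differ in either respect, a difference in adverse-event percentages mixes toxicity with length of observation.

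The distortion can run in two directions. A dose that keeps more subjects on maintenance accumulates more events at the same weekly toxicity. A dose with many early stops, including stops for toxicity under section 7-7-3, can look safer than it is. Safety is one of the two stated inputs to the recommended dose, so the percentages matter even without a test attached to them. The dose-limiting toxicity analysis does not share the problem: section 8-3-1 gives it a fixed window of 28 days.

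**Working it through.** The protocol gives no adverse-event rate, maintenance uptake or maintenance duration for this trial, so it has no figure of its own to reproduce. The observation times follow from its schedule; the incidences below are illustrations on assumed values.

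**Observation time.** The first dose falls in Week 1, so dose 8 is 7 weeks after dose 1, and Week 12 is 11 weeks after it. Doses are taken as given on schedule.

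| Subject | Last dose (weeks after dose 1) | General window (+12) | Grade 3+ non-hematologic window (+24) |
| --- | --- | --- | --- |
| 1 dose | 0 | 12 | 24 |
| 4 doses | 3 | 15 | 27 |
| 8 doses, then stop | 7 | 19 | 31 |
| Maintenance, last dose 24 weeks after dose 9 | 11 + 24 = 35 | 47 | 59 |

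The last column reads the 24 weeks as counted from the last dose. The ratio of maintenance to eight-dose observation is 47/19 = 2.5 in general and 59/31 = 1.9 for Grade 3+ non-hematologic events.

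**Illustration.** Assumed, and not in the protocol:
- the same constant hazard in both dose groups;
- incidence p0 = 30% over 19 weeks;
- maintenance uptake of 20% in one group and 50% in the other;
- 24 weeks from dose 9 to the last dose, and everyone else stopping at dose 8.

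Incidence among maintenance subjects: p1 = 1 − (1 − 0.30)^(47/19) = 0.586.

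Group incidence = (1 − uptake) × p0 + uptake × p1:
- 20% uptake: 0.8 × 0.30 + 0.2 × 0.586 = 0.357
- 50% uptake: 0.5 × 0.30 + 0.5 × 0.586 = 0.443

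The difference is (0.50 − 0.20) × (p1 − p0) = 0.30 × 0.286 = 8.6 points, with identical toxicity per week.

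**Range.** With the same uptake contrast:
- 10% base incidence, 12 weeks of maintenance (window 35): p1 = 1 − 0.9^(35/19) = 0.176; difference 0.30 × 0.076 = 2.3 points.
- 30% base incidence, 36 weeks (window 59): p1 = 1 − 0.7^(59/19) = 0.670; difference 0.30 × 0.370 = 11.1 points.
- Grade 3+ non-hematologic window, 10% over 31 weeks, 24 weeks of maintenance: p1 = 1 − 0.9^(59/31) = 0.182; difference 0.30 × 0.082 = 2.5 points.
- Equal uptake and duration: the uptake factor is zero, so the difference is zero whatever the hazard.

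**Sampling error for scale.** With 20 per group and a 30% rate, the 95% half-width of a difference is 1.96 × √(2 × 0.3 × 0.7 / 20) = 28 points.

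**Common window.** From dose 1 to Week 12 (11 weeks), the same hazard gives 1 − 0.7^(11/19) = 18.7% in both groups, whatever the uptake. Even a subject given one dose is scheduled for 12 weeks of observation. The window therefore lies inside every subject's planned follow-up, barring death or withdrawal.

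**The case against.** The strongest reply is that this belongs in the statistical analysis plan. Section 11-4 defers detailed methods to that document, which was not available here, and a tabulation window or an exposure-adjusted rate is ordinary content for it. That stands in part: the protocol does not forbid a split by period, and the separate plan may already contain one. But the protocol does state a summary, namely all events as numbers and percentages per group, and it states the window over which events are collected. Read together, these put maintenance-period events into the same percentage. The point concerns that stated method, not a missing detail.

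A reader might infer that the trial expects maintenance uptake to differ by dose, and hence that the safety comparison is biased. The documents do not support this. The dose rationale in section 7-1 expects 0.1 mg/kg, the low dose of Phase Ib, to eliminate regulatory T cells. No passage predicts that stable disease, the subject's wish or the investigator's judgement will vary with dose.

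Nor is a formal safety comparison planned. There is no test, contrast or threshold for adverse events, and the dose is chosen by a comprehensive review whose members can see onset and dosing dates. If only 0.1 mg/kg is tolerated, there is one group and nothing to compare.

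The constant hazard is also generous to the concern. Dosing falls from weekly to every 4 weeks, and the last 12 weeks are off drug. Infusion reactions, expected in almost all patients, occur early and leave little room for inflation. These objections limit the size and certainty of the effect. They do not remove the dependence of observation time on outcomes after allocation.

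**Conclusion.** The point holds in conditional form. The stated percentages can mislead the safety input to the recommended dose if maintenance uptake, maintenance duration or early stopping differs between the randomised doses. Whether any of them will differ is unknown from the protocol, so it would be wrong to say that the comparison is biased.

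On the assumed values the distortion is 8.6 points, with 2 to 11 points over the range tried. It is smaller for events that cluster at the first infusions. All of these values are well below the sampling error of about 28 points, so the distortion would seldom decide the dose on its own. It is nevertheless systematic and avoidable, and it bears on a primary endpoint. The change is a cheap improvement, not the repair of a demonstrated error.

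**What to change.** In section 11-4 1)(2):

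1. Add an adverse-event table by dose group over a window common to all subjects, from first dose to Week 12 and before any ninth dose. Name it as the table used for comparing doses.
2. Add a second table of all events after that window, to the end of each subject's observation period, for every subject whether or not on maintenance. Split it by maintenance status and give events per subject-week.
3. Keep the all-period table alongside.

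The second table must include subjects who never receive a ninth dose. If it began at dose 9, their events after Week 12 would appear only in the all-period table, and section 10-5-2 warns that severe skin disorders can appear several weeks after treatment ends.

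The cost is two extra tables from dates already recorded on the case report form. The drawback is that late events must be read across tables, and the comparison table alone does not describe delayed toxicity.

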**12. Conducting genomic and genetic analyses**

**12-1. Objectives**

Genomic and genetic analyses as described in "8-3-3 Definitions of other items 1) Common to Phase Ia and Phase Ib (8) Gene analysis (optional)" will be performed using samples collected from subjects based on appropriate consent for the purpose of exploratory and basic investigations of the efficacy and safety of the investigational drug.

**12-2. Sample handling**

Samples for genomic/genetic analysis shall be blood samples collected in accordance with "9-1. Clinical Trial Schedule".

When samples collected from subjects are sent to the laboratory (see Appendix 1 "Clinical Trial Implementation System"), to ensure their anonymity, all identification of subjects will be done only by subject identification codes.

Samples should be stored under appropriate conditions in a designated laboratory under strict conditions until requested by the Clinical Trial Coordinating Committee. During the storage period, periodic checks should be made to ensure that the samples are being properly stored, and records should be kept until disposal. When disposing of the samples, they should be disposed of appropriately in accordance with the regulations of the laboratory, and a written report of the disposal of the samples should be submitted to the medical institution.

If the laboratory conducting the genomic/genetic analysis is different from the laboratory storing the samples, the procedures for sending the samples should be established and followed. Regarding the storage of samples, the samples should be stored strictly under appropriate conditions until requested by the Clinical Trial Coordinating Committee, and during the storage period, it should be periodically checked that the samples are properly stored, and records should be kept until disposal. When disposing of the samples, they should be appropriately disposed of in accordance with the regulations of the laboratory where the genomic/genetic analysis is performed, and the results should be reported in writing to the medical institution performing the genomic/genetic analysis.

**12-3. Analysis methods**

To explore genomic biomarkers that may predict the clinical response of mogamulizumab and the development of toxicity (autoimmune adverse events: skin rash, interstitial pneumonia, etc.), a genome-wide association study (GWAS) using gene polymorphism analysis and copy number analysis using DNA derived from peripheral blood mononuclear cells before the start of treatment was conducted. Genome-wide association study (GWAS) using DNA derived from peripheral blood mononuclear cells before the start of treatment and copy number analysis, and comprehensive expression analysis of miRNA in serum will be conducted.

**12-4. Consent for sample provision**

The use of samples for genome/gene analysis will be explained sufficiently in advance to the prospective subjects, and their written consent will be obtained. Points to be noted at that time are shown in "5-3. Even if a subject withdraws his/her consent to participate in a clinical trial, the samples collected up to that point may, in principle, be used for genomic/genetic analysis. The following is a brief description of the use of samples for the purpose of genome/gene analysis. Upon receiving a written request from a subject to withdraw consent for the use of a sample for genomic/genetic analysis, the sample and results pertaining to the subject shall, in principle, be disposed of after ensuring anonymity, and a written report to that effect shall be made to the subject via the implementing medical institution. However, if the test results have already been published in a paper or the like at the time of withdrawal of consent, they cannot be discarded.

